## Discussion

The LION protocol was designed as a sham-controlled, participant-masked randomized controlled trial evaluating effectiveness of MBLT to improve self-reported and objective aspects of sleep quality, with subsequent potential “downstream” effects evaluated in neurobehavioral function, cognition, mood, and quality of life, and blood/sweat based-biomarkers of inflammation in Veterans with mTBI. This project was sponsored by MTBI^2^ and is entering its final year of enrollment and data analysis. At the time of this interim analysis for feasibility and acceptability, we have completed data collection in ~80% (n = 104) of the proposed target sample (*n* = 120).

LION was originally conceived as, and initiated in, an in-person format typical for device-based randomized controlled trials. However, in response to the COVID-19 pandemic, this protocol was revised to enable its execution in a fully remote capacity. The remotely executed randomized clinical trial format is innovative in and of itself, but especially so considering this protocol was implemented within the VA. Indeed, success with this current design was the result of many years of preparation in establishing standard operating procedures, integrating VA regulatory, clinical, the Office of Information Technology, information security/privacy, biomedical, mailroom, and other services within the local and national VA system, as well as refinement of the protocol to reduce burden and enhance the participant experience. Specific aspects of this study protocol that were novel and logistically critical to its success include: 1) The implementation of an electronic digital signature service (DocuSign) for obtaining informed consent. This enabled research coordinators to screen, consent, and schedule future visits all on essentially the first point of contact, capitalizing on participant motivation and minimizing the potential for errors or PHI/PII exposure. 2) Establishing the logistical workflow for shipping equipment to and from participants’ place of residence in a manner that minimized participant burden and enabled transfer of biospecimens. 3) Effective utilization of video conferencing technology. 4) Establishing multiple recruitment modalities to effectively reach participants nationwide. 5) Leveraging the digital distribution (via TWILIO^™^ and REDCap) of key outcome measures (e.g., all participant questionnaire data and sleep diary entries), with automatic data entry directly into REDCap.

The present rate of participant retention (83%) either exceeds or is on par with other randomized clinical trials of similar scale and complexity, e.g., Lam et al: 81% [28]; Youngstedt et al: 68% [45]. Additionally, these metrics should also be viewed in the context of this protocol being in a fully remote format, which could potentially introduce additional sources of error and/or opportunity for drop out. Accordingly, the present interim analysis refutes this possibility, demonstrating strong protocol feasibility for the remote implementation of morning bright light therapy in Veterans.

Figs 4 and 5 illustrate the spread across primary sleep related outcomes in terms of participants who were <100% adherent in each metric. In each metric there was a small subset of participants who fell below the 70% threshold for adherence. This subset of participants was further explored, and we found that there were no participants who were consistently non-adherent across all metrics, implying that it would not be straightforward to exclude whole participants from analyses, but rather partial exclusion may need to be explored. For example, within the lightbox arm across all 6 metrics (pre/post sleep diary, pre/post actigraphy, and self-report vs objective device adherence), there were n = 21 and n = 5 participants who were non-adherent in 1 or 2 metrics, and n = 1 who was non-adherent in 3 metrics, but zero participants were non-adherent in all metrics. Interestingly, of participants who were non-adherent in only 1 metric, in ~50% of those participants (n = 10) this was with respect to the objective determination of device adherence. In line with the prespecified Intention To Treat analysis, these participants will need to be retained in analyses. Within the sham arm, there were n = 9 and n = 4 participants who were non-adherent in 1 or 2 metrics, and no participants who were non-adherent in 3, 4, or 5 metrics (note that there was no objective determination of device adherence for the sham condition). There was a relatively even spread across metrics in these participants, i.e., in no single outcome were participants significantly less adherent.

Secondary outcomes in the proportion of participants with complete data were the entire self-reported questionnaire battery, neurocognitive assessment, DLMO, and biospecimen sample. For each of these metrics, all study groups at all time points report ≥75% data completeness defined as 1) no missing questions in the questionnaire battery, 2) all cognitive assessment tests complete, 3) seven DLMO salivettes for each time point, and 4) sweat and/or blood samples for each time point. The majority of outcomes were ≥83% complete, with many at 100%. Only one category, non-TBI sham participants post-intervention, reported a lower than expected rate of biospecimen sampling (60%). This is a small subset of participants (n = 10 in total), and thus, likely reflective of normal variability rather than potential bias in study coordinator/participant interaction. In summary, this interim analysis demonstrated that in the current sample of n = 104 participants, we have complete data in key outcome measures in >90% of participants, which also aligns with 80–85% of the sample reporting full device compliance. Thus, remotely implementing this randomized controlled trial has not introduced any significant increase in missingness or data incompleteness.

An additional benefit extending from the remote implementation of this trial was our ability to extend recruitment to anyone within the United States. This greatly increased our reach and anecdotally expanded enrollment to participants who would otherwise be unable or unwilling to participate in research. Similarly, nationwide recruitment also conferred a significantly greater degree of racial and ethnic diversity than would otherwise be feasible to accomplish with recruitment confined to the Portland, OR / Vancouver, WA metro area. Indeed, 34.9% of participants identified as female, 23.6% identified as belonging to a racial minority group, and 9.4% identified as Hispanic or Latino. According to the US Census Bureau (2021), 10% (~1.67 million) of Veterans identify as female, 25.8% (~4.17 million) identify as an individual from a racial minority group, and 8.6% (~1.4 million) identify as Hispanic or Latino. Thus, the present trial generally met or exceeded these US Census Bureau defined Veteran demographic statistics. Appreciating that the nationwide Veteran demographic will continue to increase in racial/ethnic diversity over time, we will continue to prioritize recruiting these traditionally under-represented populations.

In conclusion, the present study protocol described the remote implementation of a placebo-controlled participant-masked randomized controlled trial within the VA. Herein we outlined the process by which the remote implementation was achieved and highlight overall study feasibility and acceptability through an interim analysis describing a high degree of participant compliance, device adherence and meeting criteria for providing complete data across all time points. Indeed, remotely implementing a randomized controlled trial imposed significant challenges but this did not compromise data fidelity, integrity, or completeness, as evidenced by the feasibility data reported herein. Data collection is on track to be completed by September 2024 with full efficacy analyses and future directions/applications forthcoming.

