#### Flyers, social media, and radio

Flyers were placed in high traffic areas of the main VAPORHCS hospital and at two outpatient clinics and shared with local clinicians, study sponsors and other partners for broad dissemination. A social media post for LION was placed on the MTBI^2^ blog that also contributed participants to the overall TROOPS referral program. Other approved social media venues included Craigslist advertisements, GovDelivery (a marketing subscription email service), and other VA-approved accounts. IRB-approved visual banners and audio ads that aired on local AM radio stations were also utilized to recruit participants within the Portland-metro area. See Table 1 for the number of participants recruited via each approach.

**Table 1 pone.0305305.t001:** Interim demographic information for participants who have completed this protocol.

	MBLT (*n* = 69)		Sham (*n* = 35)	
	mTBI (*n* = 47)	No TBI (*n* = 22)	mTBI (*n* = 24)	No TBI (*n* = 11)
**Age,** *years*	53.2 ± 13.1	53.2 ± 14.8	50.9 ± 14.6	57.9 ± 15.9
**Education,** *years*	16.4 ± 1.9	15.8 ± 2.1	15.2 ± 1.9	16.2 ± 1.9

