### Statistical analyses

The statistical analysis plan was designed to be carried out using GraphPad Prism v9 or R, with alpha defined *a priori* at 0.05, using a thorough descriptive analysis of participant baseline characteristics prior to evaluation of outcomes. Categorical variables will be described using frequencies and percentages. Histograms and boxplots will be used to assess the distribution of continuous variables. Continuous variables that follow an approximately normal distribution will be summarized using means and standard deviations; skewed continuous variables will be reported as medians and interquartile ranges. Potential covariates will also be summarized with descriptive statistics and graphs. As part of our descriptive analyses, we will compare participants who complete versus drop out of the study by baseline characteristics and study arm to ascertain potential biases that may impact this and future studies. Effect size estimates will be reported as Cohen’s d (small = 0.2; medium = 0.5; large = 0.8) or standardized regression coefficients (β) (small = 0.14; medium = 0.39; large = 0.59). We will also report the number needed to treat (NNT) approximated using methods described by Kraemer and Kupfer [71]. The Benjamini-Hochberg procedure will be used to control the false discovery rate for primary outcomes. Statistical outliers will be identified using regression diagnostics to estimate Cook’s Distance, and then a cutoff of 4/n (n = number of participants) will be used to identify outliers. Outliers will be examined for data entry errors, but otherwise retained in analyses. If data violate parametric assumptions via Shapiro-Wilk test, test statistics will be derived using robust standard errors. We will use the intent-to-treat principle and include all participants randomized to treatment irrespective of treatment compliance.

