**Primary Sleep Outcome**				
Insomnia severity index				
Pre-intervention	47 (100%)	22 (100%)	24 (100%)	11 (100%)
Post-intervention	43 (91%)	17 (77%)	21 (88%)	10 (91%)

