**Secondary Outcomes**				
Full questionnaire battery				
Pre-intervention	47 (100%)	22 (100%)	24 (100%)	11 (100%)
Post-intervention	43 (91%)	17 (77%)	20 (83%)	11 (100%)
Cognitive Assessment				
Pre-intervention	47 (100%)	22 (100%)	24 (100%)	11 (100%)
Post-intervention	45 (96%)	22 (100%)	23 (96%)	11 (100%)
DLMO				
Pre-intervention	40 (85%)	18 (82%)	21 (88%)	10 (91%)
Post-intervention	38 (81%)	19 (86%)	20 (83%)	11 (100%)
Biospecimen sample				
Pre-intervention	41 (87%)	19 (86%)	21 (88%)	9 (82%)
Post-intervention	40 (85%)	17 (77%)	20 (83%)	6 (55%)

Data are presented as mean ± standard deviation, or *n* (%). Pre-intervention assessments span a maximum of 14 days. Post-intervention assessments and device adherence spans a maximum of 28 days. DLMO, dim light melatonin onset.

With respect to participant retention, of the *n* = 140 participants who have provided informed consent, *n* = 24 have withdrawn or been terminated (Fig 3), and therefore *n* = 116 (83%) have been retained. At the time of this interim analysis, complete pre- and post-intervention data has been recorded in n = 104 participants and therefore the remaining n = 12 participants have been randomized/allocated and are currently ongoing.

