In establishing protocol acceptability, we first considered the rate of missing data and other errors present in major outcome assessments, within the 14-day baseline period. This was examined via participant response rates for sleep diary entries and actigraphy usage (Fig 4A and 4B). Response rates for daily sleep diary entries did not differ between the active (97%) and sham (86%) conditions (*p*>0.05). Similarly, the number of days participants provided usable actigraphy data did not differ between the active (91%) and sham (89%) conditions (*p*>0.05). Protocol acceptability specific to the intervention examined overall fidelity adherence, which has averaged 83–93% across study arms. No differences were detected in the rates of participants meeting threshold for fidelity adherence across study arms when referencing either self-report or the objective assessment (*p*>0.05). Noting that there was not an objective assessment of device adherence to the sham condition. This protocol’s *a priori* definition of “fully adherent” was that participants engage with the device on at least 70% of the intervention period (5 out of every 7 days; therefore, a minimum total of 20 out of 28 days). Accordingly, device adherence has on average exceeded expectations with most adherent participants reporting device use for >23/28 days (Fig 5A and 5B).

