**Fig 5 pone.0305305.g005:**
[figure not shown]
Intervention adherence. Device use (self-report and objective), sleep diary and actigraphy data collected during intervention (over 28 days) in the active (**A**) and sham (**B**) conditions. The dashed line indicates the 70% threshold for adherence (20 days). Each data point represents a single participant and corresponds to the number of days they have complete data.

With respect to our primary outcome (ISI score), >95% of participants in both study arms have provided both pre- and post-intervention data. Supplemental sleep related outcomes included wrist-based actigraphy and sleep diary entries, the completeness for both of which was expressed in terms of the number of days with full/usable data (i.e., out of a maximum of 14 days for the baseline period and out of a maximum of 28 days for the intervention period). For both actigraphy and sleep diaries, we reported >83% of participants have complete data, defined as a minimum of 10 days of data recorded at baseline (Fig 4A and 4B) and 20 days of data recorded during the intervention period (Fig 5A and 5B), reflecting >70% of days for both periods.

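### Completeness and adherence are scored only in the 104 protocol completers, and the stated >90% (and >95% for the ISI) fails even there: Table 3 gives 91/104 = 87.5%

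*Protocol article*

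**What the plan says.** Feasibility and acceptability are the trial's stated secondary aim (Overview and ethics). The Results measure feasibility by retention, and acceptability by device adherence together with data completeness in Table 3.

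- **Who is counted.** Table 1 uses the same 69 + 35 = 104 people as Table 3 and is captioned "Interim demographic information for participants who have completed this protocol". The text after Table 3 says that "complete pre- and post-intervention data has been recorded in n = 104 participants". It also reports 140 consented, 24 withdrawn or terminated, 116 (83%) retained and 12 still ongoing.
- **Completeness claims.** For the ISI, the Results say that ">95% of participants in both study arms have provided both pre- and post-intervention data". The Discussion says that "in the current sample of n = 104 participants, we have complete data in key outcome measures in >90% of participants".
- **Adherence claim.** Full adherence is defined per participant as device use on at least 20 of 28 days. The Results then say that "device adherence has on average exceeded expectations with most adherent participants reporting device use for >23/28 days".
- **Analysis population.** Statistical analyses commits the trial to "include all participants randomized to treatment irrespective of treatment compliance".
- **Missing-data rule.** The same section handles missing data by amount: best-case and worst-case imputation below 5%, multiple imputation from 5% to 25%, and complete-case reporting without imputation above 25%.

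**The concern.** Two faults lie on top of each other.

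The first is plain inconsistency. The completeness figures in the text cannot be obtained from Table 3, and 13 of the 104 participants counted as having complete pre- and post-intervention data have no post-intervention ISI.

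The second is the denominator. A participant randomised and then lost is outside Table 3, so neither completeness nor adherence there moves when such losses rise. The adherence sentence adds a further condition by describing days of use among people who already meet the adherence definition.

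The Discussion relies on these figures when it concludes that remote delivery has not increased missingness. The missing fraction also decides how missing primary-outcome data will be handled, so a wrong fraction could lead to the wrong branch of the rule.

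**Working it through.** **Inputs.** Post-intervention ISI counts from Table 3 are 43/47, 17/22 (MBLT) and 21/24, 10/11 (sham). Pre-intervention ISI is 100% in every cell, so the post-intervention count is also the count with both. Consented 140, withdrawn or terminated 24, ongoing 12 (Results).

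**Stated retention.** (140 − 24)/140 = 116/140 = 82.9%, which reproduces the stated 83%. Also 116 = 104 + 12.

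**Stated ISI completeness, on the article's own 104.**
- All: 43 + 17 + 21 + 10 = 91; 91/104 = 87.5%.
- MBLT: 60/69 = 87.0%. Sham: 31/35 = 88.6%.
- More than 90% would need at least 94 people (0.90 × 104 = 93.6). More than 95% would need at least 99 (0.95 × 104 = 98.8).

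Neither claim reproduces, pooled or by arm.

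**Other post-intervention counts out of 104.** Questionnaire battery 91 (87.5%), cognition 101 (97.1%), DLMO 88 (84.6%), biospecimen 83 (79.8%). Only cognition exceeds 90%.

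**Adding losses after randomisation.** Randomisation followed the two-week baseline, so some of the 24 may never have been randomised. Let k be the number lost after randomisation, and assume none of them gave a post-intervention ISI. Completeness = 91/(104 + k); the 12 ongoing are excluded.

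| k | Completeness | Missing |
|---|---|---|
| 0 | 87.5% | 12.5% |
| 6 | 82.7% | 17.3% |
| 12 | 78.4% | 21.6% |
| 18 | 74.6% | 25.4% |
| 24 | 71.1% | 28.9% |

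No value of k gives 90%.

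**What the abstract implies for k.** It puts drop-out below 10% of those enrolled. Over those consented, 24/140 = 17.1%, which does not fit. If enrolled means randomised, the rate is k/(116 + k): 12/128 = 9.4% and 13/129 = 10.1%, so k is at most 12 and completeness lies between 78.4% and 87.5%.

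**Missing-data branch.** More than 95% complete means less than 5% missing, the first branch. Table 3 means 12.5% missing, the second. The second still holds at k = 17 (91/121 = 75.2%, 24.8% missing); the third is reached only from k = 18.

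**Adherence.** Mean self-reported use in the 104, weighted from Table 3: (22.8 × 47 + 24.6 × 22 + 22.1 × 24 + 23.5 × 11)/104 = 2401.7/104 = 23.1 days (82%). With leavers at zero days, a lower-bound assumption, it is 2401.7/116 = 20.7 days (74%) at k = 12 and 2401.7/128 = 18.8 days (67%) at k = 24.

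**The case against.** The strongest reply has five parts.

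1. **Drop-out is disclosed.** The 24 leavers and the 83% retention stand next to Table 3, and the Discussion compares retention with other trials. This is correct. A reader might infer that the article hides attrition; it does not. What stands is narrower: the acceptability measures themselves do not respond to loss after randomisation.
2. **There is no acceptability rule to pass.** A reader might infer a criterion that is met however many people leave. The article states no trial-level pass mark; its adherence threshold applies to each participant. Nor are the Table 3 percentages high by construction: one ISI cell is 77% and one biospecimen cell is 55%.
3. **The 71% is a bound.** It needs all 24 to have been randomised and none to have given a post-intervention ISI. The documents do not show this.
4. **The adherence evidence does not rest on one sentence.** The mean days of use in Table 3 are not conditioned on adherence, and all four exceed 20. The conditioned sentence is poor wording beside usable figures.
5. **The >90% might mean something else.** The key outcome measures are not listed. Pooling pre- and post-intervention ISI records gives (104 + 91)/208 = 93.8%. But that is a share of assessments, whereas the sentence speaks of participants, and it still falls short of 95%.

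It is also fair to say that an interim descriptive table does not alter the intent-to-treat commitment for efficacy, and that the missing-data branch will be settled on the final data.

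**Conclusion.** The point holds in this form. The stated completeness figures are wrong on the article's own denominator: 87.5% for the primary outcome, against claims of more than 90% and more than 95%. This needs no assumption.

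The denominator is also too favourable, because it consists of people described as protocol completers. How much this matters depends on k: completeness lies between 71.1% and 87.5%, or between 78.4% and 87.5% if the abstract's drop-out figure refers to randomised participants. Both ranges assume that leavers gave no post-intervention ISI.

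For the primary analysis, the text and Table 3 imply different branches of the missing-data rule. A reader might go further and infer that the 25% limit has been passed; that requires k of 18 or more, which the documents do not establish and which the abstract's figure, read over randomised participants, would exclude.

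**What to change.** - Report data completeness, and the proportion reaching 20 of 28 days, by arm with 95% confidence intervals, over all randomised participants past the assessment window. Count those lost after randomisation as missing where they gave no outcome, and count their device use up to exit. Exclude the 12 ongoing and show losses before randomisation separately.
- Replace the sentence on days of use among the adherent with the unconditional figures.
- Reconcile the abstract's drop-out rate (<10% against 24/140 = 17.1%), the statement that 104 have complete data, the ISI row of Table 3, the >95% in the Results and the >90% in the Discussion. Say which outcomes count as key.
- State that the missing fraction used to choose the missing-data branch is taken over all randomised participants.

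The cost is a recount of data already held and some rewording. Reported completeness and adherence will be less favourable.

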## Results

Formal statistical analyses across participant groups (Tables 1 and 2) or in primary/secondary outcomes have not yet been explored given the ongoing/incomplete status of this randomized controlled trial. However, a central goal of presenting this study protocol was to evaluate overall feasibility and acceptability. This was best demonstrated through evaluating overall participant retention (feasibility; Fig 3) and a combination of protocol fidelity adherence and “data completeness” for primary outcomes (acceptability; Table 3).

**Table 3 pone.0305305.t003:** Feasibility and acceptability.

	MBLT (*n* = 69)		Sham (*n* = 35)	
	mTBI (*n* = 47)	No TBI (*n* = 22)	mTBI (*n* = 24)	No TBI (*n* = 11)

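### The Discussion's claim of complete key outcome data in more than 90% of participants conflicts with Table 3, where 87.5% have the post-intervention primary outcome; joint completeness is not reported

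*Protocol article*

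**What the plan says.** The Results say that acceptability was shown through "a combination of protocol fidelity adherence and “data completeness” for primary outcomes (acceptability; Table 3"). The thresholds are set one measure at a time. Full adherence means that "participants engage with the device on at least 70% of the intervention period" (20 of 28 days). Diary and actigraphy completeness is "defined as a minimum of 10 days of data recorded at baseline", with 20 days during the intervention.

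Results are then given by measure. For the ISI, the Results claim that more than 95% of participants in both arms gave pre- and post-intervention data. For diary and actigraphy, they claim that more than 83% of participants were complete.

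The Discussion adds counts across metrics. In MBLT, over six metrics (diary pre/post, actigraphy pre/post, self-reported and objective device use), "there were n = 21 and n = 5 participants who were non-adherent in 1 or 2 metrics", and one participant failed three. "Within the sham arm, there were n = 9 and n = 4 participants who were non-adherent in 1 or 2 metrics", with none failing more of that arm's five metrics.

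The Discussion summarises that "we have complete data in key outcome measures in >90% of participants" and that 80–85% reported full device compliance. It closes by citing participants "meeting criteria for providing complete data across all time points".

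**The concern.** The summary sentence is worded as a share of participants, and the closing sentence speaks of completeness across time points. The figures behind them are rates for single measures. When failures fall on different people, such rates can all look high while fewer participants are complete on everything. In addition, the post-intervention ISI row of Table 3 alone lies below 90%.

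Feasibility and acceptability are the trial's stated secondary aim (Overview and ethics) and the main conclusion of this article, which reports no efficacy result. A team planning a similar remote trial would take the 90% figure as its expected yield of complete participants. The ISI rate also matters within this plan. The Statistical analyses section chooses the missing-data method by the fraction missing, and the 95% claim and Table 3 point to different bands.

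**Working it through.** **Inputs.** Table 3: group sizes 47, 22 (MBLT, total 69) and 24, 11 (sham, total 35); post-intervention counts by group. Discussion: MBLT 21, 5 and 1 participants failing one, two and three metrics; 10 of the 21 failed only objective device use; sham 9 and 4 failing one and two.

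**1. Can the stated figure be reproduced?** Post-intervention participants from Table 3:
- ISI: 43 + 17 + 21 + 10 = 91; 91/104 = 87.5% (MBLT 60/69 = 87.0%, sham 31/35 = 88.6%)
- Questionnaire battery: 43 + 17 + 20 + 11 = 91; 87.5%
- Cognition: 45 + 22 + 23 + 11 = 101; 97.1%
- DLMO: 38 + 19 + 20 + 11 = 88; 84.6%
- Biospecimen: 40 + 17 + 20 + 6 = 83; 79.8%

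Only cognition exceeds 90%. Other routes above 90% answer different questions:
- Average pass rate over metrics: failures are 21 + 2×5 + 3×1 = 34 of 69×6 = 414, and 9 + 2×4 = 17 of 35×5 = 175, so 1 − 51/589 = 91.3%.
- Participants failing at most one metric: (104 − 5 − 1 − 4)/104 = 94/104 = 90.4%.
- ISI assessments pooled over both time points: (104 + 91)/208 = 93.8%.

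None of these is the share of participants with complete key outcome data.

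**2. The 95% claim for the ISI.** Neither arm reaches it (87.0%, 88.6%), nor does any of the four subgroups (91%, 77%, 88%, 91%). The missing fraction is 13/104 = 12.5%. That falls in the plan's 5–25% band (multiple imputation), whereas more than 95% complete would fall below 5% (best- and worst-case imputation).

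**3. Diary and actigraphy jointly (four metrics).** The article does not give this, but its counts bound the number failing at least one.
- MBLT maximum: 27 − 10 = 17, since ten failed only objective device use. Minimum: 1, since only the three-metric failure must include a data metric (there are two device metrics).
- Sham maximum: 9 + 4 = 13. Minimum: 4, since each two-metric failure must include a data metric (there is one device metric).
- Total failing: 5 to 30. Complete on all four: 74/104 to 99/104, that is 71.2% to 95.2%.

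**4. Adding the ISI (13 missing).**
- No overlap with diary or actigraphy failures: (104 − 30 − 13)/104 = 61/104 = 58.7%.
- Full overlap: 91/104 = 87.5%.

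The upper limit stays below 90% whatever the overlap.

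**5. Threshold met on every metric.**
- MBLT: 69 − (21 + 5 + 1) = 42/69 = 60.9%
- Sham: 35 − (9 + 4) = 22/35 = 62.9%
- Overall: 64/104 = 61.5%

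MBLT counts for four or five failed metrics are not stated, so 64 is an upper limit. Counting the ten MBLT participants who failed only objective device use as passing gives 74/104 = 71.2%.

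**The case against.** A reader might infer that acceptability was defined jointly and that only 62% met the definition. The documents do not support this. The word used, "a combination of protocol fidelity adherence and" completeness, can mean two kinds of evidence considered together. Table 3 is laid out by metric, and no section requires a participant to pass every one.

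Nor can 62% replace the 90% figure. It includes device use (twice in MBLT, once in sham), which the Discussion reports separately from data completeness, and it omits the ISI. For diary and actigraphy alone the bounds are 71–95%, which contain values above 90%.

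A reader might also infer that participants below 70% have no usable data. That does not follow either. The actigraphy analysis uses three to five nights near the end of each period, the mixed models use all observed data, and intention to treat retains non-adherent participants.

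Finally, the article prints the cross-metric counts and gives the figure of more than 83% for diary and actigraphy, so nothing is concealed.

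All of these points stand, and they limit the finding to a misstated completeness figure and an unreported joint rate. They do not rescue the 90% sentence, because the ISI is the designated primary outcome and its own row in Table 3 is at 87.5%.

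**Conclusion.** The statement that more than 90% of participants have complete data in key outcome measures is not supported by the article's own figures. With the ISI among those measures, the share is at most 87.5%. With diary and actigraphy as well, it lies between about 59% and 87.5%. The Results' figure of more than 95% for the ISI conflicts with the same table row.

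Separately, at most 62% met the 70% threshold on every device-use, diary and actigraphy metric. That rate is unreported; it does not show that a criterion was missed.

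The conclusion assumes that Table 3's post-intervention counts are correct, that the ISI is a key outcome measure, and that the 104 participants are the denominator, as the sentence says. The lower limit of 59% further assumes that no MBLT participant failed four or five metrics. The upper limit does not depend on this.

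**What to change.** - In the Discussion's summary of completeness, replace the 90% figure with one that agrees with Table 3. In the Results, do the same for the 95% ISI figure. If Table 3 is the part in error, correct the table instead.
- Add one row to Table 3, by arm, for participants jointly complete on pre- and post-intervention ISI, diary and actigraphy.
- Report the share meeting the threshold on every metric beside the single-metric rates, with its metric set named and preferably on a set common to both arms. Do not present it as the data-completeness rate.
- Qualify the concluding phrase on complete data across all time points in the light of the joint row. Table 3 covers only the pre- and post-intervention assessments.

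The 90% phrase does not occur in the Abstract or the concluding paragraph, so it needs no replacement there.

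The cost is one table row and a few reworded sentences from data in hand, and a less favourable headline figure.
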